#### Analysis

In addition to the study measures, additional data collected from the EHR will include demographics (age, marital status, race/ethnicity, insurance status) and medical co-morbidity. Planned data analyses include bivariate analyses of baseline data to compare demographic and clinical characteristics of the two intervention groups. In order to examine the success of randomization, t-tests and chi-square tests will be used to check for between-group equivalence. For each dependent variable, intent-to-treat longitudinal analyses will be conducted and outcomes for the two intervention groups will be compared. Mixed-design analysis of variance (repeated measures ANOVA with a between-subjects factor) tests will assess for within-group changes over time and for significant differences between the MBIC + DEF and MBIC + SE groups for each of the various outcome measures. Between-group differences in the likelihood in engagement in depression treatment (depression treatment and other treatment modalities) will be tested through chi-square tests followed by binary logistics regression modeling. Engagement in treatment will be dichotomously coded. All tests will be two-tailed with *p* < 0.05 used to determine significance. Study aims 1 and 2 will be tested for the MBIC + DEF versus MBIC + SE. All models will be checked for the need for additional covariates (demographic and clinical baseline characteristics) and interaction terms. Analyses will use all available data (i.e. intent-to-treat analyses) from participants with baseline data, post education (DEF or SE) visits and 12-month follow-up visits.

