The evaluation of Aim 1 will examine the specific effects of the MBIC + DEF to increase knowledge about depression, reduce stigma, and increase engagement in depression treatment compared to MBIC + SE as measured by the following:Changes in knowledge of depression among Hispanic patients pre and post DEF compared with SE, as measured by the DKM. The DEF group is expected to report significantly greater DKM scores over time when compared with the SE group indicating gains in depression knowledge following receipt of depression education.Changes in attitudes among Hispanic patients toward depression pre and post DEF compared with SE using the SCMHC, LSAS, and the SD measures. The DEF group is expected to report significant changes in SCMHC, LSAS, and the SD over time when compared to the SE group and reported reductions in stigma related to mental health and psychiatric medications following depression education.Determine engagement in depression treatment for patients in DEF vs. SE.Quantify the number of patients diagnosed with depression and received the DEF intervention who went on to begin depression treatment compared with SE. The DEF group is hypothesized to have a greater portion of individuals engaging in depression treatment than the SE group following treatment. Furthermore, participants in the DEF group will have an increased likelihood of later engaging in treatment following the intervention.Quantify which treatment modality the patient with depression chose after the DEF compared to SE: pharmacotherapy; counseling; or other behavioral intervention. The DEF group is hypothesized to have a greater portion of individuals engaging in pharmacotherapy, counseling, or other behavioral interventions than the SE group following treatment. Furthermore, participants in the DEF group will have an increased likelihood of later engaging in pharmacotherapy, counseling, or other behavioral interventions following the depression.

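### Aim 1 compares the arms on five main outcomes, each at p < 0.05 with no primary outcome or error control, and the models leave covariates open while not fixing adjustment for baseline

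*Protocol article*

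**What the plan says.** All references are to the Data analysis part of the protocol article.

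- **Significance rule (Analysis).** "All tests will be two-tailed with *p* < 0.05 used to determine significance". No adjustment or ordering of outcomes is stated.
- **Scope (Analysis).** "Study aims 1 and 2 will be tested for the MBIC + DEF versus MBIC + SE". The mixed-design ANOVA tests "for significant differences between the MBIC + DEF and MBIC + SE groups for each of the various outcome measures".
- **Model content (Analysis).** "All models will be checked for the need for additional covariates (demographic and clinical baseline characteristics) and interaction terms". There is no list of covariates and no criterion for including one. Separately, "t-tests and chi-square tests will be used to check for between-group equivalence".
- **Aim 1.** Each outcome has its own hypothesis. For knowledge: "The DEF group is expected to report significantly greater DKM scores over time when compared with the SE group". For stigma: "The DEF group is expected to report significant changes in SCMHC, LSAS, and the SD over time", again relative to SE. DEF is also expected to do better on entry into treatment and on the treatment modalities chosen. None of these is called primary.
- **Aim 2.** Change in PHQ-9 from baseline to 12 months is named as the primary outcome. DEF is also expected to have more patients with a 5-point drop.
- **Sample size.** The calculation is for depression scores only, at a two-sided 5% level.

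**The concern.** The abstract and the discussion present the trial as a test of whether the fotonovela reduces stigma and improves depression literacy and treatment uptake. Those are Aim 1 questions, and Aim 1 is where error is not controlled. A reader who sees one of five Aim 1 results below 0.05 cannot tell from the plan whether it answers the aim or is the chance result to be expected from that many tests.

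Two features of the models add to this. The final covariates and interaction terms are settled only once the models have been examined, so more than one analysis of each outcome remains open. And the covariate most likely to help, the baseline value of the outcome, is not fixed in the model. Baseline enters only through a change score (PHQ-9) or as one level of the repeated factor (mixed ANOVA), and both use it less efficiently than adjustment does.

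**Working it through.** **The plan's own figure.** The article gives no overall error rate. Its only related figure is 56 per arm for effect size 0.57, 80% power, two-sided 5%. Recalculation gives 49 (normal approximation) or 50 (t-test); 56 corresponds to about 85% power. The difference is on the cautious side and does not affect this point. What matters here is that the trial was sized for one comparison at 0.05, on depression scores.

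**Counting the arm comparisons.**
- Aim 1 main outcomes: DKM, SCMHC, LSAS, SD, any engagement = 5.
- Aim 1 modalities: pharmacotherapy, counseling, other behavioral intervention = 3 if tested separately, 1 if tested together.
- Aim 2: PHQ-9 change and 5-point response = 2.
- Total 10, or 8 with modality as one test. The 50% reduction under Aim 2 is a benchmark, not clearly an arm comparison, and is not counted.

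**Chance of at least one false positive, no true effect.** For k independent tests: 1 − 0.95^k in either direction, and 1 − 0.975^k in DEF's favour.

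| k | Either direction | Favouring DEF |
|---|---|---|
| 5 (Aim 1 main) | 1 − 0.95^5 = 22.6% | 1 − 0.975^5 = 11.9% |
| 8 | 33.7% | 18.3% |
| 10 | 1 − 0.95^10 = 40.1% | 1 − 0.975^10 = 22.4% |

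Correlation between outcomes is not given, so a range is assumed. Simulation with equally correlated normal test statistics gives:
- k = 5, correlation 0.5: 18% in either direction.
- k = 10, correlation 0.3 / 0.5 / 0.7: 35% / 29% / 21% in either direction; 18% / 14% / 11% favouring DEF.

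**Open model choice.** The article gives no rule, so its effect cannot be derived. A simulation with assumed inputs (150 patients, six baseline covariates, together explaining 20% of outcome variance) shows how much depends on the rule used, per outcome:
- Covariates kept for association with the outcome: 5.5% two-sided error.
- Covariates kept for baseline imbalance: 4.9%.
- The set most favourable to DEF kept: error favouring DEF rises from 2.5% to about 6.8%.
- The strongest of the main effect and six interactions reported: about 30% in either direction.

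**Precision from baseline.** Assume equal variance σ² at baseline and at 12 months, and correlation ρ between them.
- Raw change: variance 2σ²(1 − ρ).
- Adjusted for baseline: variance σ²(1 − ρ²).
- Ratio: (1 − ρ²) / [2(1 − ρ)] = (1 + ρ)/2.
- ρ = 0.3, 0.4, 0.5, 0.6 gives 0.65, 0.70, 0.75, 0.80, a reduction of 35%, 30%, 25%, 20%.

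The values of ρ are assumptions. The comparison is with raw change at a single time point.

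**The case against.** **A primary exists, and the tests overlap.** PHQ-9 change is named primary for Aim 2 and is the basis of the sample size; that test alone carries 5% error if its model is fixed. Any engagement is largely the union of the modalities, and the 5-point response is derived from PHQ-9 change. This stands: ten independent tests is an upper bound, and the gap lies mainly in Aim 1.

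**A reader might infer that a chance DEF benefit is likely.** The figures do not support that. The 40% is below even odds, assumes independence and counts differences in both directions. In DEF's favour it is about 22% at most from multiplicity alone, and 11% to 18% at correlations of 0.7 to 0.3.

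**A reader might infer that the baseline tests select the covariates, or that models are chosen by their treatment result.** The article says neither. The baseline tests are described as a check on randomization, and ordinary selection rules leave error near 5%. Inflation from model choice is a possibility that the wording leaves open, not a demonstrated error.

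**A reader might infer that any one significant Aim 1 result will count as success.** No success rule is stated. The fault is that nothing says how five results will be read together.

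**This is detail for an SAP.** Covariate lists and model formulas often are, and no SAP is shown. But the article itself fixes 0.05 for every test and a data-checked choice of model. The concern is with those stated rules.

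**Baseline is already in the repeated-measures ANOVA.** True, but as an outcome level. Adjusting for it is an efficiency gain rather than the repair of an invalid test, and the 20% to 35% figure is not shown for the scales measured at five time points.

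**Conclusion.** The point holds for Aim 1. With five main outcomes, each at 0.05, and no primary, the chance of at least one false-positive arm difference in either direction is about 23% under independence and 18% at an assumed correlation of 0.5. Over all ten comparisons it is at most about 40%, about 22% favouring DEF, and less with correlated outcomes. The primary PHQ-9 comparison is not compromised by multiplicity.

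Unspecified covariates and interactions could raise these figures, by an amount that cannot be taken from the article. Leaving out adjustment for baseline forgoes a variance reduction of 35% to 20% against raw change at one time point, for assumed correlations of 0.3 to 0.6. This is worth correcting and needs only wording; it does not call the design into question.

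**What to change.** Specify before data lock:

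1. **One model per outcome**: arm plus the baseline value of that outcome. Engagement has no baseline value, so use baseline PHQ-9 there.
2. **No data-driven covariate selection**: the model in step 1 replaces it. Label interaction terms exploratory.
3. **Aim 2**: keep 12-month PHQ-9 as primary at two-sided 0.05, in line with the sample size.
4. **Aim 1**: apply Holm across DKM, SCMHC, LSAS, SD and engagement. With step 3, this controls error within each aim, not across the trial, and the plan should say so.
5. **Modalities and responder rates**: report estimates with confidence intervals and no significance claim.

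No new data are needed: the Measures/Assessments section already schedules the four Aim 1 scales at baseline and the PHQ-9 at screening.

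The cost is a stricter threshold for Aim 1. Holm's first step is 0.05/5 = 0.01. For illustration, take the plan's effect size of 0.57, which was derived for depression scores and is only assumed for Aim 1. With 56 per arm, power is Φ(0.57 × √(56/2) − 1.960) = Φ(1.056) = 85% at 0.05, and Φ(3.016 − 2.576) = Φ(0.440) = 67% at 0.01; 72 evaluable per arm would give 80% at 0.01. Later Holm steps are less strict. Baseline adjustment offsets part of this for the four scales. No such offset has been shown for engagement.

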#### Randomization

After a patient screens positive for depression with the iPad Depression Screening application, the provider will immediately facilitate an introduction to the DCM for potential enrollment in the study. The DCM will assess for the presence of the nine diagnostic criteria for major depression from the Diagnostic and Statistical Manual of Mental Disorders (DSM-IV) [41] through a clinical interview. Once the depression diagnosis is confirmed, patients will be offered the opportunity to participate in the study, guided through the informed consent process and randomized to one of two treatment groups. A block randomization list that randomizes 150 participants into 75 blocks will be generated through an online randomization website and will be kept in a locked filing cabinet in the DCM’s office. Patients will be assigned to the group that coordinates with their patient enrollment number on the randomization list. One hundred and fifty patients will be randomly assigned to two possible treatment arms: (1) MBIC + DEF; or (2) MBIC + SE. A randomization log will be maintained by the Project Coordinator, which will include treatment assignment, names of participants, and participant identification numbers.

At the baseline visit, the DCM will have the patient complete all study measures and engage the patient during the regular intake process. The DCM will document the patient’s PHQ-9 screening score, the stigma measures, current treatment preferences (pharmacotherapy, counseling), and potential barriers to care in a research database. The DCM will also explain the compensation schedule, which includes payment for completing measures after the education intervention and each follow-up research visit, and schedule the patient’s education visit and first MBIC appointment to take place after the education visit.

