#### Education

Within one week, patients will return to the clinic to complete their education session and study measures with a research assistant – either SE or DEF, depending on the group to which the patient was randomized. Two bilingual research assistants, hired from the school of social work, will be assigned and trained to deliver the different education interventions (one each, without exposure to the other education materials). Patients will be encouraged to bring family members or loved ones to the education session. Each education session will be provided in English or Spanish, depending on patient preference, and will conclude with compensation to the patient upon completion of the study measures.

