##### Follow-up visits

Patients will return to the clinic to complete all study measures and be compensated at the following time points: one-month post education session, six months post enrollment, and 12 months post enrollment. Between follow-up visits, research personnel will contact patients monthly to remind them of study participation and future appointments. If patients do not return for their follow-up visits, data will be collected from their medical record to include PHQ-9 scores and medication information, if available.

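### The analysis set labelled intent-to-treat is defined by attending the post-education and 12-month visits, so read literally it is a completer analysis

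*Protocol article*

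**What the plan says.** The Analysis section of the protocol article first states the principle: "For each dependent variable, intent-to-treat longitudinal analyses will be conducted and outcomes for the two intervention groups will be compared". It names the method: "Mixed-design analysis of variance (repeated measures ANOVA with a between-subjects factor) tests will assess for within-group changes over time" and for differences between the two groups. It closes by saying whose data are used: "Analyses will use all available data (i.e. intent-to-treat analyses) from participants with baseline data, post education (DEF or SE) visits and 12-month follow-up visits".

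The order of events comes from two earlier sections. Under Randomization, patients with a confirmed diagnosis are "guided through the informed consent process and randomized to one of two treatment groups". Under Education, the session is a separate, later appointment: "Within one week, patients will return to the clinic to complete their education session and study measures with a research assistant".

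Under Follow-up visits, the protocol plans for patients who are lost: "If patients do not return for their follow-up visits, data will be collected from their medical record". The items named are PHQ-9 scores and medication information, where available.

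For engagement (Aim 1), one line reads: "Quantify the number of patients diagnosed with depression and received the DEF intervention who went on to begin depression treatment compared with SE". Neighbouring lines in the same list compare the DEF and SE groups as wholes.

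**The concern.** Intent-to-treat means that every randomized patient is analysed in the arm assigned. The closing sentence of the Analysis section instead attaches that label to patients who have a post-education visit and a 12-month visit. Both are attended, or missed, after randomization. A set chosen that way is no longer protected by randomization.

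The choice matters here because returning to clinic is close to what the trial measures. Aim 1 concerns engagement in treatment and Aim 2 concerns retention and remission, and the Analysis section tests both aims between the arms. The sentence governs the Aim 2 primary outcome (PHQ-9 change from baseline to 12 months) as well as the knowledge and stigma comparisons. Patients who leave early may differ in depression outcome from those who stay. If they leave more often, or for different reasons, in one arm, the comparison of stayers is distorted.

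There is also a practical loss. Early assessments of patients who miss the 12-month visit would go unused, as would the record data collected for exactly those patients.

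**Working it through.** **1. What the closing sentence selects.** The visits qualify the participants, are joined by *and*, and are three in number. Set against the order of events:

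| Condition | Timing relative to randomization |
|---|---|
| Baseline data | At enrollment |
| Post-education visit | After, at a return visit within a week |
| 12-month visit | After, 12 months from enrollment |

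Two of the three conditions are post-randomization attendance. If the list is read as time points rather than as conditions on patients, it omits the one-month and six-month visits, at which the knowledge and stigma scales are also given. It would then not be all available data. On neither reading does the sentence say that all 150 patients are analysed as assigned.

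**2. What the method adds.** As usually run, repeated-measures ANOVA needs a value at every modelled time point and drops patients without one. The Analysis section makes no provision that offsets this.

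**3. Patients left out.** Inputs from the Sample size section: 150 randomized; 25% attrition assumed; 6–18% cited from a systematic review. Equal arms of 75 are inferred from 150 participants in 75 blocks.

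- At 25%: 150 × 0.25 = 37.5, about 38 left out; 75 × 0.75 = 56.25 per arm remain.
- At 6%: 150 × 0.06 = 9 left out.
- At 18%: 150 × 0.18 = 27 left out.

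**4. Power.** Two-sample t-test, two-sided 5%, effect size 0.57. The plan's own figure does not reproduce: 80% power needs 49.3, so 50 per group, not 56. The stated 56 corresponds to about 85% power. That is a separate matter and does not affect this point.

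| Per arm | Power |
|---|---|
| 56 | 0.848 |
| 75 (complete outcomes) | 0.934 |

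**5. Bias in a completer contrast.** Let d be the dropout fraction in an arm and g the amount, in SD, by which dropouts do worse than completers. The completer mean is then too favourable by d × g, and the contrast is off by d₁g₁ − d₀g₀. With a common g this is g(d₁ − d₀). The values of d and g below are assumed:

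- 25% vs 25%: g × 0 = 0.
- 30% vs 20%, g = 0.25 to 0.5: 0.025 to 0.05 SD.
- 35% vs 15%, g = 0.25 to 0.5: 0.05 to 0.10 SD, or 9–18% of 0.57.

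**6. Engagement denominator.** Assume that 60% of education attenders engage in each arm, that no non-attender does, and that attendance is 80% (DEF) and 90% (SE). Among the educated the difference is 60% − 60% = 0. Among all randomized it is 0.60 × 0.80 − 0.60 × 0.90 = 0.48 − 0.54 = −6 percentage points. The denominator can therefore change the answer.

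**The case against.** The best defence is that the sentence is loosely worded rather than restrictive. The word *only* does not appear in it, it speaks of all available data, and intent-to-treat is promised separately for every outcome. Retrieving records for patients who do not return would be pointless if a missed visit meant exclusion. This stands to the extent that the document contradicts itself, and one cannot assert that the investigators firmly intend to exclude these patients. It does not rescue the sentence, whose plain reading still defines the set by attendance.

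Four stronger readings are tempting, and the documents do not support them.

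- *Anyone missing any of the five assessments is dropped.* The article does not say which time points enter the ANOVA. If 5–10% also missed each of three further visits, 75 × 0.75 × 0.95³ = 48.2 or 75 × 0.75 × 0.90³ = 41.0 per arm would remain, with power of about 0.79 or 0.72. That rests on an unstated model and on assumed independent losses, whereas missed visits tend to cluster in the same patients. With 25% attrition alone, power stays above the planned 80%.
- *A large false PHQ-9 difference is to be expected.* Dropout of 25% in each arm, related to outcome in one arm only (log-odds 0.5–1.0 per SD, SD 5.5, all assumed), gives about 0.65 to 1.17 points (0.12–0.21 SD) under no true effect. This is a one-sided scenario. If dropout depends on the unobserved 12-month score, a mixed model that assumes missing at random would not in general remove it.
- *Engagement is counted only in educated patients.* The wording about receipt stands in one line, for one arm, with no denominator stated. The lines around it refer to whole groups.
- *Selection at the education visit is selection on the effect of DEF.* Attendance precedes exposure to the content, so the content cannot have changed it.

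**Conclusion.** The point holds as a contradiction that must be resolved. The Analysis section promises intent-to-treat and, on its plain reading, defines a completer set. The named ANOVA reinforces this, and the record data planned under Follow-up visits have no clear place in it.

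The consequence that can be sized from the protocol's own figures is the exclusion of about 38 of 150 randomized patients at 25% attrition, or 9 to 27 at 6–18%. Power at 0.57 is then about 85%, against about 93% if all 75 per arm had complete outcomes. The trial would not become underpowered on its own assumptions; the main issue is validity. Bias depends on dropout differing between arms in amount or in its relation to outcome. Its size cannot be known from the documents, and it is zero if dropout is the same in both arms in both respects.

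On engagement, the finding is limited to inconsistent wording of who is counted. Confidence is high on the contradiction and low on any particular size of bias.

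**What to change.** - Replace the closing sentence of the Analysis section with: all randomized patients, analysed in the arm assigned, using every available assessment including record-derived PHQ-9.
- Replace the repeated-measures ANOVA with a likelihood-based linear mixed model for repeated measures, with the 12-month contrast between arms as the estimate for PHQ-9. This is valid under missing at random, so add a sensitivity analysis for departures from that assumption.
- State that the engagement denominator is all randomized patients in both arms, and reword the Aim 1 line that refers to receipt of the intervention so that it agrees with its neighbours.
- Keep the analysis of patients with all visits as a sensitivity analysis only.

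Covariance structure and covariates can be left to the statistical analysis plan. The cost is wording and slightly more analysis work. No patients or visits are added, and record retrieval is already planned. The change should be made before data lock.

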**Methods:**

We are conducting a randomized controlled trial among 150 depressed adult Hispanics in a primary care safety net setting, testing the effectiveness of a culturally appropriate depression education intervention to reduce stigma and increase uptake in depression treatment among Hispanics, and implement a Measurement-Based Integrated Care (MBIC) model with collaborative, multidisciplinary treatment and culturally tailored care management strategies.

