### Aims and objectives

The study aims to examine a novel culturally adapted patient education intervention to increase engagement by Hispanics in depression treatment. The intervention will be implemented after diagnosis using an innovative screening technology and via measurement-based integrated care for the treatment of depression, which will have a substantive impact on reducing mental health disparities in the Hispanic population.

#### Specific aim 1

Examine the specific effects of a Depression Education *Fotonovela* (DEF) to increase knowledge of depression, reduce stigma, and increase engagement in depression treatment among Hispanic patients.

#### Specific aim 2

Evaluate the impact of measurement-based integrated care (MBIC) on retention in treatment and remission of depression symptoms in one community-based Federally Qualified Health Center (FQHC) in North Texas whose patient population is majority Hispanic.

#### Specific aim 3

Examine the feasibility of universal screening and accurate detection of depression among adult primary care patients utilizing innovative iPad Depression Screening technology.

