### Intervention

The study will compare outcomes among patients randomly assigned to one of two treatment conditions: (1) MBIC with DEF (MBIC + DEF); or (2) MBIC with standard education (MBIC + SE). All patients enrolled in the Measurement, Education and Tracking in Integrated Care (METRIC) study will receive MBIC. The schedule of enrollment, interventions, and assessments is outlined in Fig. 1, study flow is outlined in Fig. 2, and page listings for all study components can be found in the Standard Protocol Items: Recommendations for Interventional Trials (SPIRIT) Checklist (see Additional file 1).

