#### Measurement-based integrated care

As part of MBIC, patients will meet with the DCM every 1–4 weeks, depending on their treatment plans, to complete brief psychotherapy interventions. Mental health measures and medication response and adherence will be collected using the iPad Depression Screening and Monitoring application and will be recorded in the EHR.

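### The engagement outcome is counted among patients who attended after randomisation, which conflicts with the promised intent-to-treat analysis and can leave out the least engaged patients

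*Protocol article*

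**What the plan says.** Raising treatment uptake is part of the trial's stated purpose. The Abstract (Methods) speaks of an intervention to "reduce stigma and increase uptake in depression treatment among Hispanics", and Specific aim 1 includes the goal to "increase engagement in depression treatment among Hispanic patients".

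The Analysis section gives the count for that goal: "Quantify the number of patients diagnosed with depression and received the DEF intervention who went on to begin depression treatment compared with SE". It adds that "Engagement in treatment will be dichotomously coded", to be tested by chi-square and then logistic regression. A further item splits the chosen treatment into pharmacotherapy, counselling or another behavioural intervention.

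On the analysis set, the same section promises intent-to-treat longitudinal analyses for each dependent variable. Its closing sentence then equates intent-to-treat with the available data from participants who have baseline data, post-education visits and 12-month visits.

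On timing, the Randomization section has patients randomised once diagnosis is confirmed and consent given. The depression care manager (DCM) then books the "education visit and first MBIC appointment to take place after the education visit". The Education section puts the education session at a return visit within one week. The allocation list is kept in the DCM's office.

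On care common to both arms, the Intervention section says "All patients enrolled in the Measurement, Education and Tracking in Integrated Care (METRIC) study will receive MBIC". The Measurement-based integrated care section says patients meet the DCM every 1–4 weeks "to complete brief psychotherapy interventions".

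**The concern.** Coming back for the education session is itself an early act of engagement, and it happens after randomisation. A count restricted to those who received the education, or to those also seen at 12 months, can leave out the patients whose failure to take up treatment the outcome is meant to register. The comparison is then no longer between the randomised groups. If attendance differs by arm, the result can be wrong in either direction.

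A second, lesser matter is what counts as beginning treatment. Every enrolled patient is booked into MBIC, whose visits contain psychotherapy, and counselling is a listed modality. If one attended MBIC visit is enough, most patients in both arms could be coded as engaged, leaving little room for the arms to differ.

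**Working it through.** **Plan's own figure.** There is none to reproduce. The Sample size section rests on depression scores, and no engagement rate, attendance rate or power for engagement is stated. The inputs taken from the article are 150 randomised (75 per arm), two-sided 5%, and a chi-square test. Every rate below is an assumption.

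**Step 1: order of events.** Consent and randomisation come first, then the education visit (within one week), the first MBIC appointment, and follow-up to 12 months. Education attendance and 12-month attendance therefore both follow randomisation.

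**Step 2: the descriptions side by side.**

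| Place in the Analysis section | Patients counted |
|---|---|
| General intent-to-treat statement | All randomised, on the usual meaning |
| Closing sentence on available data | Those with baseline, post-education and 12-month visits |
| Aim 1 engagement item | Those who received the education |

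The second and third rows depend on attendance and do not match the first.

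**Step 3: what the denominator can do.** Let *a* be the proportion attending education and *b* the proportion of attenders who begin treatment. Count non-attenders as not engaged. The rate among all randomised is then *a × b*.

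- Attendance 90% (DEF) v 80% (SE), *b* = 90% in both. Among attenders: 90% − 90% = 0 points. Among all randomised: 0.90 × 0.90 = 81% v 0.80 × 0.90 = 72%, a difference of 9 points.
- Same attendance, but 72% of all randomised begin treatment in both arms, all of them attenders. Among all randomised: 0 points. Among attenders: 0.72/0.90 = 80% v 0.72/0.80 = 90%, an apparent 10 points against DEF.
- Attendance 90% in both arms, *b* = 90% in both. The difference is 0 points on either denominator.

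The attendance-based count can thus hide a difference or create one. In these examples it does so only when attendance differs by arm.

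**Step 4: the possible ceiling.** Exact power of the uncorrected chi-square test, 75 per arm, two-sided 5%, by binomial enumeration:

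| Assumed SE rate | DEF rate needed for 80% power |
|---|---|
| 50% | about 72% |
| 70% | about 88% |
| 80% | about 95% |
| 90% | about 99.3% |
| 95% | not attainable; 100% gives about 52% power |

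The last row can be checked by hand. If all 75 DEF patients engage, 71/75 in SE gives chi-square = 150 × (75 × 4)² / (75 × 75 × 146 × 4) = 4.11, above 3.84. With 72/75 it is 150 × (75 × 3)² / (75 × 75 × 147 × 3) = 3.06, below 3.84. At least 4 unengaged SE patients are needed. That probability is 0.52 if 5% are unengaged and 0.95 if 10% are. With a continuity correction, the maximum power at an SE rate of 90% falls to about 77%.

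**The case against.** **The denominator wording may be loose.** The engagement item is introduced as a comparison of patients in DEF and SE, its hypothesis concerns the DEF group, and receipt of the intervention may serve only as an arm label. The closing sentence may merely list the time points that supply data. This is a fair reading. But the text also supports the attendance-based reading in two places, and the intent-to-treat label cannot settle it because the article itself explains that label by visits attended.

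**Bias is not shown.** Patients meet the education content only at the education visit, so the content cannot cause earlier non-attendance, and nothing in the article reports unequal attendance. This stands, and a reader who infers that the result will be distorted goes beyond the documents. Unequal attendance remains possible: the DCM, who books the visits, has the allocation list in the office. Attendance at 12 months comes after the education and could respond to it.

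**The ceiling is conjecture.** A reader might infer that the yes/no outcome is saturated by MBIC. The documents do not support that. A booked visit is not an attended one, and the Abstract and Background describe low antidepressant use and early withdrawal. The article does not say that one DCM visit counts as beginning treatment, and that definition may properly sit in the full protocol or SAP. Pharmacotherapy start, already listed separately, need not be near any ceiling. At SE rates of 50–70% there is no difficulty of this kind.

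**A visit count is not clearly better.** Visit frequency follows individual plans of 1–4 weeks, so a count partly reflects the plan, and it replaces the question of uptake with one of intensity. This stands.

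**Conclusion.** The denominator point holds. As written, a treatment-uptake outcome is conditioned on attendance after randomisation, against the intent-to-treat analysis promised in the same section. The size of the effect cannot be stated from the documents. The shifts of 9 and 10 points above rest on assumed attendance of 90% v 80%, and with equal attendance the illustrated shift is nil.

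The ceiling is only a caution. It depends on one attended MBIC visit counting as beginning treatment and on an SE rate of roughly 90% or more, neither of which is stated. Nor should engagement be taken for the trial's primary outcome: it is prominent in the stated purpose and in Aim 1, but the only outcome called primary is PHQ-9 change, for Aim 2.

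**What to change.** Reword the engagement item and the closing sentence of the Analysis section so that they agree with intent-to-treat:

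- Analyse engagement in all randomised patients by assigned arm, counted from randomisation.
- Keep patients who miss the education or 12-month visit in the denominator.
- Take treatment start from the medical record for everyone, and code no recorded treatment as not engaged.
- Report pharmacotherapy start as an engagement result in its own right, beside any treatment started.
- A count of attended visits may be added as a supportive analysis. It need not replace the stated outcome.

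The cost is a change of wording and some record extraction. The Follow-up visits section already plans to take medication information from the record, where available, for patients who do not return. Extraction of counselling attendance is not mentioned and would have to be confirmed. The drawback is that treatment obtained outside the clinic and not recorded there would be coded as not engaged. Treatment and recruitment are unchanged.
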